#### Cognition

##### Cognitive test battery

A comprehensive cognitive test battery (11 tests: 7 computerized (E-prime 2.0, Psychology Software Tools Inc.) 4 paper and pen; will be administered (duration: approximately 1 h) [33, 34]. The following cognitive domains will be assessed: *processing speed* (Digit symbol), *attention* (Trail Making Test-A), *working memory* (Capacity: Automated Operation Span; Backward Digit Span), *executive functions* (Trail Making Test-B, Stroop, n-back), *episodic memory* (free recall; recognition), *semantic memory* (SRB:1), and *visuospatial ability* (Form Board Test).

Additionally, subjective memory complaints will be measured using a single item [35].

#### Secondary outcomes

##### Cardiovascular fitness

Participants will undergo a sub maximal cycle ergometer test [36]. Heart rate response to a sub maximal rate of work will be used to estimate maximal oxygen consumption (cardiovascular fitness). Cardiovascular fitness will be expressed as absolute values (liter per minute) and as relative values (mL per minute per liter body mass). Before the test, blood pressure will be determined in sitting position, and a check-list will be used to assess potential contra-indications to participate in this test. In case a contra-indication would be found, such as high blood pressure, the submaximal cycle ergometer test will not be performed.

##### Body composition

Body mass index will be calculated from measured weight and height. Weight will be measured by Tanita BC-418MA Body Fat Analyzer digital scale (Tanita Corporation of America, Inc., Arlington Heights, IL) to the nearest 0.1 kg.

Waist circumference will be measured in duplicate with participants standing dressed in underwear and exhaled, at the minimum circumference between the iliac crest and the rib cage. Measurement will be rounded to the nearest 0.5 cm.

##### Sleep

During night time, participants will wear the accelerometer (Actigraph, as described above) on the non-dominant wrist. Using existing algorithms, the following key aspects of sleep will be calculated: Time to sleep onset, sleep efficiency, times wake up after sleep onset and total sleep time. Additionally, subjects will fill in a sleep diary, by noting time of day for going to bed and waking up and fill in a generic sleepiness questionnaire [37].

#### Self-reported physical activity. Sedentary behavior, and other health habits

Self-reported data for physical activity, sedentary behavior and active transport will be assessed, using three validated questions [38–40]We will assess the use of the physical activity and sedentary behavior strategies, such as the use of an app, exercising during work and walking-and standing meetingsOther health habits will be assessed, including smoking/snuss, drinking and diet [41, 42]

##### Physical health

Self-reported physical health [43] and self-reported health conditions, e.g. diabetes or intestinal disorders.

#### Working mechanisms

##### Blood analyses

Participants will be instructed to fast for at least eight hours preceding the assessment. Fasting venous blood samples will be obtained from the antecubital vein. Per measurement point, two blood samples (each 5 mL) will be drawn. Cooled (~ 4 °C) samples will be centrifuged to aquire plasma and serum, aliquoted and stored at minus 80 °C. HbA1c will be analyzed using the IFCC method [44]. Plasma and serum levels of inflammatory markers, BDNF [45, 46], VEGF [46], and IGF-1 [46] will be analyzed using enzyme-linked immunosorbent assays following manufacturer’s instructions. Furthermore, genetic profiling of BDNF genes of will be performed [47, 48]. Genomic DNA will be isolated from peripheral white blood cells using the PureGene kit (Gentra Systems, Minneapolis, MN). The Val66Met polymorphism at the BDNF locus will be genotyped using the amplification conditions reported by [49] and detection by fluorescence polarization as described by Chen et al. (1999) [50].

Questionnaires:Exercise self-efficacy [51–53], and comparable questionnaire adjusted for sedentary behaviorFor individual barriers [17] and motivation to change a questionnaire was developed based on previous qualitative research [54–56]Feasibility and acceptability of interventions (self-developed questionnaire)Self-regulation [57]Over commitment [58]Work/non-work interference and enhancement [59, 60]Job Demand-control-support [61]Job insecurity [62]Work engagement [63]Work climate [64]Health-promoting leadership [65]

Additionally, a qualitative study will be performed on feasibility and acceptability of the interventions. For quality control of the counselling intervention sessions will be recorded.

#### Co-variables

Demographic and work-related variables, including organizational changes [66]Medication

### Data management and quality assurance

All personnel involved in the trial is trained according to standard operating procedures and the principles of good clinical practice. Each participant was assigned a unique numeric identifier code before their first measurement to enable link-anonymisation of data. All personal data will be stored in encrypted files, and links to personal information are only available to the study co-ordination team. Consent forms and paper acquired data are stored in locked filing cabinets. Paper acquired data (fitness tests and part of cognitive tests) are entered by a research assistant unaware of group allocation. Random checks of the entered data against the source document are performed and outlying values are double checked with the source document. Furthermore, all data are checked on appropriate range and consistency by trained research assistants.

### Sample size

Sample size was calculated in three steps [67]:i.Sample size based on an individualized randomized controlled trialii.Corrected for the design effect, taking into account the clusteringiii.Corrected for unavailable data

The sample size calculation was based on 1 follow-up measurement, with a power of 80% and significance level of 0.05, corrected for 3 groups (0.05/3 = 0.017).

The design effect was 1.77. This was determined, assuming that the proportion of variance accounted for by between cluster variations was 0.05 [68]. Furthermore, we corrected for unequal clusters, assuming an average cluster size of 14 with a standard deviation of 5.83.

Unavailable data were assumed by correcting for the drop out of 3 clusters, with an average cluster size of 14 per group and for unavailability of data (missing, individual drop-outs) for 20% of participants.

For the remaining input of the sample size calculations, data were used from subproject 1 of the larger research project (as described earlier).

Using these input, estimated needed sample sizes are the following:Physical activity, moderate to vigorous physical activity, meeting the guidelines

Proportion of participants meeting guidelines in control group: 30%.

Estimated proportion of participants meeting guidelines in intervention groups: 60%.i.*Sample size based on individualized randomization:* 52 per groupii.*Corrected for design effect:* 92 per groupiii.*Corrected for unavailable data:* 125 per groupSedentary behavior, total sedentary behavior, in hrs/day

Difference in mean value between groups: 1 h/day.

Standard deviation: 1.4 h/day.i.*Sample size based on individualized randomization:* 41 per groupii.*Corrected for design effect:* 72 per groupiii.*Corrected for unavailable data:* 101 per groupMental health, stress, single item [24]

Proportion of participants with stress complaints in control group: 26%.

Estimated proportion of participants with stress complaints in intervention groups: 5%.i.*Sample size based on individualized randomization:* 57 per groupii.*Corrected for design effect:* 100 per groupiii.*Corrected for unavailable data:* 134 per groupCognition, stroop test (in seconds)

Difference in mean value between groups: 7 s.

Standard deviation: 9.85 s.i.*Sample size based on individualized randomization:* 41 per groupii.*Corrected for design effect:* 73 per groupiii.*Corrected for unavailable data:* 102 per group

This 24- months study includes 5 measurement time points, with measurements every 6 months. The 5th measurement point will only be performed provided that drop-out rate is not higher than 30% and sufficient resources are available [69]. When persons drop-out of the study they will be asked whether they are still willing to wear the accelerometers and/or fill out a short version of the questionnaire including only the main distal outcomes.

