### Randomization

In order to control contamination and to limit interaction between the different groups, randomisation will be done on a cluster level. We aim to have 24 clusters (8 clusters per arm), 10 at Intrum and 14 at ICA-gruppen. Clusters will be composed while considering: 1) having a team or line manager, 2) having regular group meetings, 3) limited regular meetings with other teams. Block randomisation and assignment will be performed using a computer-generated random number list. Groups will be randomly allocated (1:1) with stratification for company and cluster size (large vs small). In order to implement the interventions in an order consistent with logistical capacity matched randomization will be used in case needed. Randomization will be performed after finishing first data collection and participants will be notified by email. Randomization and allocation will be performed by researchers not involved in data collection. Research assistants involved in data collection and processing will be blinded for group allocation.

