### Statistical analyses

In accordance with the research questions, statistical analyses will be conducted to determine whether the groups differ in changes over time in proximal, distal as well as secondary outcomes. Statistical significance will be set at the 5% level (two-tailed). To adjust for company and clustering, analyses will be performed using multilevel modelling. The models will include allocated group (reference group = control group) and baseline values. Both crude models and models adjusted for potential confounders will be determined. Potential confounders will be defined a priori based on the findings from the larger research project. Separate models will be made for the different outcomes regarding physical activity, sedentary behavior, mental health and cognition. All analyses will be performed using both per protocol and intention to treat approaches, were intention to treat is defined as persons attending at least 3 out of 5 counselling sessions.

Moderator analysis will examine whether intervention effects differ across individual (e.g. age, gender and education). Mediator analyses will test whether individual and organizational factors, described under working mechanisms, mediated the intervention effects.

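### The four final sample sizes appear to allow for 20% data loss by multiplying by 1.2 rather than dividing by 0.8, leaving each 3% to 4% short of the plan's own preceding step; whether power falls depends on the design effect

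*Protocol article*

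**What the plan says.** The Sample size section works in three steps: an individually randomised size, a correction for clustering, and a correction for unavailable data. The inputs are as follows.

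- Error rates: "with a power of 80% and significance level of 0.05, corrected for 3 groups (0.05/3 = 0.017"). The Statistical analyses section makes testing two-tailed.
- Clustering: "The design effect was 1.77", "assuming that the proportion of variance accounted for by between cluster variations was 0.05", with a mean cluster size of 14 and a standard deviation of 5.83.
- Losses: three clusters of average size 14 drop out, and there is a further allowance "for unavailability of data (missing, individual drop-outs) for 20% of participants".

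The per-group results are:

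| Outcome | Step i | Step ii (clustering) | Step iii (unavailable data) |
|---|---|---|---|
| Meeting activity guidelines | 52 | 92 | 125 |
| Sedentary time | 41 | 72 | 101 |
| Stress | 57 | 100 | 134 |
| Stroop | 41 | 73 | 102 |

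No formula is printed for step iii. The last Stroop entry, for instance, reads only "Corrected for unavailable data:* 102 per group". The Abstract sets the recruitment target at 110 per arm, 330 in total.

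**The concern.** If 20% of those recruited yield no data, 80% remain, so a requirement of n needs n/0.8 = 1.25n. Multiplying by 1.2 and then losing 20% returns 1.2 × 0.8 = 0.96 of n. It covers a loss of only 1 − 1/1.2 = 16.7%. If step iii was done that way, none of the four final figures restores the number printed just before it, although each is presented as already corrected for unavailable data. These figures are the trial's published sample size justification, and readers will compare them with the target of 110.

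**Working it through.** **1. Reproduce the plan's figures.**

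Step i uses a two-sided alpha of 0.017, 80% power and the normal approximation, with unpooled variance for proportions. The formula is n = (z₁₋α/₂ + z₀.₈)² × s²/d², where s² = 2·SD² for means and p₁(1−p₁) + p₂(1−p₂) for proportions.

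- Guidelines, 30% v 60%: 52.1
- Sedentary time, 1 h, SD 1.4 h: 40.9
- Stress, 26% v 5%: 56.7
- Stroop, 7 s, SD 9.85 s: 41.3

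These match the printed 52, 41, 57 and 41.

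Design effect: CV = 5.83/14 = 0.416, and 1 + ((0.416² + 1) × 14 − 1) × 0.05 = 1.771, printed as 1.77. Step ii from the unrounded values is 92.2, 72.3, 100.4 and 73.1, which matches 92, 72, 100 and 73.

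**2. Identify step iii.** Three clusters over three arms is one cluster, or 14 persons, per arm.

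| Outcome | Step ii n | 1.2n + 14 | Printed | n/0.8 + 14 |
|---|---|---|---|---|
| Guidelines | 92 | 124.4 | 125 | 129 |
| Sedentary time | 72 | 100.4 | 101 | 104 |
| Stress | 100 | 134.0 | 134 | 139 |
| Stroop | 73 | 101.6 | 102 | 105.25 (106) |

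Rounded up, 1.2n + 14 gives all four printed figures. Carrying unrounded values and rounding to nearest gives the same four. None of the other forms tried matches all four: n/0.8 + 14, (n + 14) × 1.2, (n + 14)/0.8, either inflation alone, or either inflation plus 42 (three clusters per arm).

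**3. What remains after the stated losses.** Evaluable = 0.8 × (N − 14).

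| Outcome | Evaluable | Step ii need | Short by |
|---|---|---|---|
| Guidelines | 0.8 × 111 = 88.8 | 92 | 3.2 (3.5%) |
| Sedentary time | 0.8 × 87 = 69.6 | 72 | 2.4 (3.3%) |
| Stress | 0.8 × 120 = 96.0 | 100 | 4.0 (4.0%) |
| Stroop | 0.8 × 88 = 70.4 | 73 | 2.6 (3.6%) |

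**4. Power at those numbers.** Power = Φ(d × √(evaluable/DE)/s − z), with alpha 0.05/3 (z = 2.394).

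- *Design effect held at 1.77.* For guidelines, 88.8/1.77 = 50.2 and 0.3 × √50.2/√0.45 − 2.394 = 0.774, so power is 0.780. The other three are 0.780 (sedentary time), 0.777 (stress) and 0.781 (Stroop).
- *Design effect recomputed.* If 14 is the enrolled cluster size, a 20% loss leaves 0.8 × 14 = 11.2 per cluster. The same formula with the same CV gives 1 + ((0.416² + 1) × 11.2 − 1) × 0.05 = 1.61. Power is then 0.823, 0.823, 0.820 and 0.824 in the same order.

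**5. Power at the target of 110 per arm.** Evaluable = 0.8 × (110 − 14) = 76.8.

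| Outcome | DE 1.77 | DE 1.61 |
|---|---|---|
| Guidelines | about 71% | about 76% |
| Stress | about 67% | about 72% |

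Sedentary time and Stroop are at about 82% even with a design effect of 1.77.

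**The case against.** A reader might infer that the trial claims 80% power and fails to deliver it. The documents do not support that. The 78% figure takes 20% of people out of the clusters while keeping a design effect calculated for full clusters of 14. The Study population and Randomization sections give 330 participants in 24 clusters, or 13.75 each, so 14 looks like the enrolled size. The plan also uses 14 for a whole lost cluster. On that reading the design effect falls with the loss and all four stated sizes keep about 82% power. If random loss also widens the spread of cluster sizes, the design effect is about 1.62 and the answer is the same. This objection stands against a firm claim of lost power. It does not settle the matter the other way, because the article does not say whether 14 is the enrolled or the analysed size.

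Three further points have weight. The multiplier is inferred, since no formula is printed; the inference is strong because the fit is exact for all four figures. The order of losses is not stated either: inflating the whole sum, (n + 14)/0.8, would give 133, 108, 143 and 109. And the correction moves no outcome across the target: 101 and 102 become 104 and 106, still under 110, while 125 and 134 become 129 and 139, still over it.

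What survives is the arithmetic. A requirement of 92 carried through the plan's own losses is not met by 125, and the same holds for the other three. Losing the 20% first and then 14 evaluable persons leaves fewer still (86.0, 66.8, 93.2 and 67.6).

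**Conclusion.** The point holds as an error in the stated sizes. All four step iii figures are consistent with multiplying by 1.2 and adding one cluster of 14 per arm, and all four fall 3% to 4% below the step ii requirement once both stated losses occur. Dividing by 0.8 adds 3 to 5 persons per arm. This rests on one lost cluster per arm, a 20% loss among the remaining participants, and the printed step ii figures as the requirement. If only one of the two losses occurred, the stated sizes would suffice.

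Any effect on power is conditional: about 78% with the design effect fixed at 1.77, about 82% with it recomputed at 11.2 per cluster. The gap between the target of 110 and the requirements for guidelines and stress exists without this error. The error only makes it look smaller, by 4 persons per arm for guidelines (15 rather than 19) and 5 for stress (24 rather than 29). It is a small matter, but the figures are published and easy to put right.

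**What to change.** - Print the step iii formula, including the order in which cluster loss and individual loss are applied.
- Correct it to n/0.8 + 14 and restate 129, 104, 139 and 106 per arm (Stroop is 105 if unrounded values are carried and rounded to nearest). Alternatively, recompute steps ii and iii with the design effect at the analysed cluster size, and say so.
- State whether the mean cluster size of 14 is the enrolled or the analysed size.
- Report the power achieved at 110 per arm for guidelines and stress, with the design effect used.

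The cost is four figures and a few sentences. Recruitment does not change.

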**Methods:**

a 3-arm, clustered randomized controlled trial (RCT) with waiting list control group amongst adult office-workers of two large Swedish companies. Cluster teams will be randomized into 6-month interventions or to a passive waiting list control group which will receive the allocated intervention with a 6-month delay. Two multicomponent interventions will be studied of which one focuses on improving physical activity and the other on reducing sedentary behavior. Both interventions include 5 sessions of motivational counselling. In the physical activity intervention persons also get access to a gym and team leaders will organize lunch walks and encourage to exercise. In the sedentary behavior intervention standing- and walking meetings will be implemented and team leaders will encourage to reduce sitting. The recruitment target is 110 office-workers per arm (330 in total). Measurements will be repeated every 6 months for a total intended duration of 24 months. Proximal main outcomes are physical activity measured with accelerometers and sedentary behavior with inclinometers. Distal outcomes are self-reported mental health and a cognition test battery. Additional outcomes will include cardiovascular fitness, body composition, sleep, self-reported physical activity and sedentary behavior, other health habits, physical health, and working mechanisms from blood samples and questionnaires.

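### The two yes/no sample-size lines (stress 134, MVPA guideline 125 per arm) exceed the 110 per arm to be recruited, so the stated 80% power at alpha 0.017 is not reached on those scales

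*Protocol article*

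**What the plan says.** The Sample size section works "with a power of 80% and significance level of 0.05, corrected for 3 groups (0.05/3 = 0.017"). It sizes four outcomes, two on a continuous scale and two as proportions.

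- Sitting time and the Stroop test are sized as differences in means and need 101 and 102 per arm.
- Stress, a single item, is sized as a proportion: "Proportion of participants with stress complaints in control group: 26"% against "Estimated proportion of participants with stress complaints in intervention groups: 5"%. The steps are 57, 100 and 134 per arm.
- MVPA is sized as guideline attainment, 30% in control, with "Estimated proportion of participants meeting guidelines in intervention groups: 60"%. The steps are 52, 92 and 125 per arm.

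The Abstract (Methods) states: "The recruitment target is 110 office-workers per arm (330 in total").

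The Statistical analyses section plans multilevel models with allocated group and baseline value. It does not say on which scale stress or MVPA enters the model, and it sets the test level differently: "Statistical significance will be set at the 5% level (two-tailed"). The Actigraph section derives the share of wear time in MVPA as the first of six summaries; guideline attainment is the fifth.

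**The concern.** The target of 110 covers the two continuous lines but neither of the two yes/no lines, and the article does not explain why 110 is enough for those. Stress is the only mental-health outcome that was sized, and guideline attainment is one of the two sized proximal outcomes behind the primary hypothesis. A reader would take the section to promise 80% power for both.

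The assumed stress proportion also leaves very few cases in the active arms. If stress were analysed as yes/no with clustering and a baseline term, the estimates would rest on a handful of events. Both problems come from sizing graded information as a dichotomy.

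**Working it through.** **Inputs (Sample size section).** Alpha 0.05/3 = 0.0167, taken as two-sided; power 80%; "assuming that the proportion of variance accounted for by between cluster variations was 0.05"; mean cluster size 14, SD 5.83; cluster loss; 20% unavailable data. Three lost clusters of 14 spread over three arms is 14 per arm, the reading that reproduces the stated totals.

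**Reproducing the plan's figures.**

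- k = (2.394 + 0.842)² = 10.469.
- n = (p1q1 + p2q2) × k / (p1 − p2)².
- Stress: 0.2399 × 10.469 / 0.21² = 56.95, so 57.
- MVPA: 0.45 × 10.469 / 0.30² = 52.3, stated as 52.
- Design effect: CV = 5.83/14 = 0.416; 1 + ((0.1734 + 1) × 14 − 1) × 0.05 = 1.771. The plan agrees: "The design effect was 1.77".
- Stress: 57 × 1.77 = 100.9 (stated 100); 100 × 1.2 + 14 = 134.
- MVPA: 52 × 1.77 = 92.0; 92 × 1.2 + 14 = 124.4, so 125.

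**What 110 per arm leaves.** Undoing the plan's own inflation gives (110 − 14)/1.2 = 80. Removing 20% after the cluster gives (110 − 14) × 0.8 = 77. Removing it before gives 110 × 0.8 − 14 = 74. On the plan's own scheme, 80 compares with the 100 and 92 required.

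**Power at alpha 0.0167.** Divide by the design effect: at 77, n_eff = 77/1.771 = 43.5.

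- Unpooled, stress: SE = √(0.2399/43.5) = 0.0743; 0.21/0.0743 − 2.394 = 0.43; power 67%.
- Unpooled, MVPA: SE = √(0.45/43.5) = 0.1017; 0.30/0.1017 − 2.394 = 0.55; power 71%.
- The pooled version replaces 2.394 × SE by 2.394 × √(2p̄q̄/n_eff), with p̄ the mean of the two proportions.

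| Analysed per arm | Stress, pooled–unpooled | MVPA, pooled–unpooled |
|---|---|---|
| 74 | 61–65% | 65–69% |
| 77 | 63–67% | 67–71% |
| 80 | 65–69% | 69–73% |

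**Expected stress cases.** Active arm: 74 × 0.05 = 3.7 to 80 × 0.05 = 4.0. Control arm: 74 × 0.26 = 19 to 80 × 0.26 = 21. In a beta-binomial simulation with 7 teams of 11 (one reading of the planned loss) and an intracluster correlation of 0.05, on average 4.5 of 7 teams in an active arm had no case, and the arm had two or fewer cases in about 31% of runs.

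**At the 5% level.** k = 7.849. Stress: 0.2399 × 7.849/0.0441 = 42.7, so 43; × 1.77 = 76.1; 76 or 77 × 1.2 + 14 = 105 to 107. MVPA: 0.45 × 7.849/0.09 = 39.2; × 1.771 = 69.5; × 1.2 + 14 = 97. Stress power at 74–80 analysed is about 77–82%.

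**Graded stress (assumption: a uniform shift on a normal underlying scale).**

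- 26% to 5% is z(0.95) − z(0.74) = 1.645 − 0.643 = 1.00 SD.
- n = 2 × 10.469/1.00² = 21; × 1.771 = 37.2, so 38; 38 × 1.2 + 14 = 59.6, about 60 per arm. Power at 74–80 analysed is about 99%.
- Proportional-odds calculations with the common odds ratio (0.26/0.74)/(0.05/0.95) = 6.7 and seven assumed control distributions of three to five levels give about 55–80 per arm.
- The shift giving 80% power at 77 analysed is 3.236 × √(2 × 1.771/77) = 0.69 SD. At 77, 0.6 SD gives about 66% and 0.5 SD about 47%.

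**The case against.** The strongest reply is that nothing commits the trial to a yes/no analysis. The proportions appear only as sizing inputs, the Statistical analyses section names no scale, and the list of mental-health measures gives no cut-off. If the analysis is graded, binary sizing is conservative rather than wrong. This stands: a reader might infer that stress is planned as a dichotomy, and the document does not say so. The choice of scale may properly sit in an analysis plan not shown here.

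A reader might also infer that MVPA is reduced to guideline met or not met. The Actigraph section contradicts that.

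Third, sparse events need not break the model. In 400 simulated trials with 7 teams of 11 per arm, 26/5/5%, intracluster correlation 0.05 and an assumed baseline correlation of 0.5, about 7% had an active arm with no cases. In the rest, a random-intercept logistic model converged with usable estimates. So failure is an occasional risk, not the expected result.

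Fourth, the shortfall depends on alpha 0.017, and stress is one of nine mental-health measures under the secondary hypothesis. Both are correct.

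None of this removes the mismatch between the section's own requirements and its target. If the analysis is binary, the stated power is not reached at the stated alpha. If it is graded, these two lines do not describe it.

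**Conclusion.** The point holds as a mismatch between stated power and recruitment. At alpha 0.017, 110 per arm gives about 61–69% power for stress and 65–73% for guideline attainment, against a stated 80%, with about 4 stress cases per active arm. This rests on the protocol's own proportions, design effect and loss allowances; the ranges reflect how the losses are applied and which variance formula is used. At an uncorrected 5% the MVPA shortfall disappears and the stress line is about met, so the two sections must be reconciled before the size of the gap is settled.

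It would go too far to say that a graded stress analysis would meet the stated power. The documents give neither the item's number of response levels nor a standard deviation, and the 1.00 SD shift is back-calculated from the proportions. Power is about 99% at 1.0 SD, 80% at about 0.69 SD, and lower for smaller shifts. No comparable gain is claimed for MVPA, because the documents give no distribution for it.

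**What to change.** - In the Sample size section, restate the power that 110 per arm provides for the stress and guideline lines, or explain why the target is acceptable below their requirements.
- Use one significance level in the Sample size and Statistical analyses sections, and say whether the three-group correction applies to the tests.
- State that the main stress analysis uses the item's full response scale in an ordinal or linear mixed model with the baseline score, provided the item has three or more levels, and that MVPA is analysed as a share of wear time. Report both proportions alongside.
- Restate the two sizing lines on those scales, with the stress power shown over a range of shifts and the assumptions named.

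The cost is wording and a short recalculation; no new data, visits or participants are needed. The small downside is that the main effect becomes a shift in score rather than a difference in proportions.
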